### Sample size {14}

Under simple randomisation, to detect a medium effect size of Cohen’s *d* = 0.5 with 90% power for 5% significance with one baseline measure and two follow-up measures, with correlation between these of 0.6 [38], 37 participants per arm are required. The adjusted standard deviation obtained from this calculation is 0.663 (step 1).

To estimate the power for a design with clustering in one arm only, we used the following parameters: 6 therapists each with a caseload of 8 participants completing follow-up assessments, an intracluster correlation coefficient (ICC) of 0.05 [39], an equally sized group (for maximum efficiency) of 6 × 8 = 48 unclustered participants for the treatment as usual arm (ICC = 0), a 5% significance level, adjusted variance from Step 1, i.e. 0.663, a medium effect size of Cohen’s *d* = 0.5. This resulted in an estimated power of 88%.

We assume 26% attrition so the sample size to be recruited is 96/(1 − 0.26) = 130 participants, i.e. 65 per group implying a caseload of between 10 and 11 participants per therapist over the course of the intervention.

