## Statistical methods

### Statistical methods for primary and secondary outcomes {20a}

Participant flow through the trial will be shown in a chart according to the CONSORT Statement 2010. Baseline sociodemographic characteristics and outcomes will be summarised by trial arm using descriptive statistics appropriate to distribution. The primary analysis will be conducted using a mixed effects model with clustering by therapist in the intervention group only and control participants forming their own clusters of size 1. We will include fixed effects for PSYRATS-AH Distress at baseline, the stratification variable (site) and allocation and a random effect for therapist/control participant and a random effect to account for repeated observations within participants. A small sample correction (e.g. Satterthwaite’s) will be applied due to the small number of therapists. We will report the adjusted difference in mean PSYRATS-AH Distress between arms, its 95% confidence interval and p value at each time point. Statistical significance is set at the 5% level.

Secondary outcomes will be analysed using mixed effects models appropriate to outcome distribution controlling for baseline voice hearing distress (PSYRATS-AH). A detailed statistical analysis plan will be written by the CTU Statistician and Trial Statistician, agreed with the research team and reviewed by the Trial Steering Committee (TSC).

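### The sample size applies the therapist ICC of 0.05 to an already reduced variance, so the stated 88% power holds only if that ICC is conditional on baseline and averaging, which the text does not say

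*Protocol article*

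**What the plan says.** Sample size {14} works in two steps.

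Step 1 ignores clustering. For d = 0.5 it targets 90% power at the 5% level. The repeated-measures assumption is stated as "with one baseline measure and two follow-up measures, with correlation between these of 0.6". Step 1 arrives at 37 per arm and then reports: "The adjusted standard deviation obtained from this calculation is 0.663 (step 1").

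Step 2 adds clustering in the intervention arm only: 6 therapists with 8 completers each, 48 unclustered controls, a therapist ICC of 0.05 taken from a cited source, d = 0.5, and the "adjusted variance from Step 1, i.e. 0.663". The result is given as: "This resulted in an estimated power of 88" per cent. The scale of the ICC (raw outcome, baseline-adjusted, or averaged over follow-ups) is not stated, and neither is the formula or the degrees of freedom.

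Statistical methods {20a} describes the analysis: baseline distress, site and allocation as fixed effects, "a random effect for therapist/control participant and a random effect to account for repeated observations within participants", and a small-sample correction such as Satterthwaite's because there are few therapists.

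**The concern.** An ICC is a proportion of a particular variance. Applying 0.05 to the Step 1 variance assumes that baseline adjustment and averaging shrink the therapist component as much as they shrink the rest.

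- **Baseline adjustment.** Randomisation follows the baseline assessment, and the assistant psychologists are told of their participants only after that (Sequence generation {16a}, Implementation {16c}). A covariate measured before any therapist contact cannot absorb a therapist effect on the outcome.
- **Averaging.** The model in {20a} has one therapist effect shared by both follow-ups. The mean of two follow-ups carries that effect in full.

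Only six therapists deliver the intervention, so therapist variance is a main influence on precision. If 0.05 is not already on the adjusted scale, the calculation gives it too little weight and the stated power is too high. The two labels for 0.663 add to the difficulty, because a reader cannot tell from the text alone which quantity entered Step 2.

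**Working it through.** **Inputs from {14}:** d = 0.5 in raw SD units; 5% significance (sidedness not stated; two-sided reproduces the figures); one baseline and two follow-ups with correlation 0.6; 6 × 8 = 48 against 48; ICC 0.05. **From {20a}:** one therapist effect across follow-ups, Satterthwaite-type correction.

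**Step 1 reproduced.** Variance factor = (1 + 0.6)/2 − 0.6² = 0.80 − 0.36 = 0.44, and √0.44 = 0.663. Per arm, n = 2 × (1.96 + 1.2816)² × 0.44 / 0.5² = 36.99, so 37. Both stated figures match. Hence 0.663 is the SD and the variance is 0.44.

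**Step 2 formula.** Let vT be the therapist variance, vI the individual variance in the intervention arm and vC the control variance.

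- a = vT/6 + vI/48, b = vC/48, SE = √(a + b), noncentrality = 0.5/SE
- df = (a + b)² / (a²/5 + b²/47)
- power from the noncentral t, two-sided 5%

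**Step 2 reproduced.** vT = 0.05 × 0.44 = 0.022, vI = 0.418, vC = 0.44. Then a = 0.012375, b = 0.009167, SE = 0.1468, noncentrality 3.41, df 14.3, power 88.7%. A simulation of 200,000 trials gives 88.0%, so the stated 88% is recovered. The design effect is 1 + 7 × 0.05 = 1.35.

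**Therapist variance on other scales.** The total intervention-arm variance is held at 0.44, so vI = 0.44 − vT.

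| What the 0.05 refers to | vT | ICC on the 0.44 scale | Design effect | SE | df | Power |
|---|---|---|---|---|---|---|
| Baseline-adjusted mean of both follow-ups | 0.05 × 0.44 = 0.022 | 0.050 | 1.35 | 0.1468 | 14.3 | 88.7% |
| One baseline-adjusted follow-up | 0.05 × 0.64 = 0.032 | 0.073 | 1.51 | 0.1517 | 13.2 | 86.2% |
| Unadjusted mean of two follow-ups | 0.05 × 0.80 = 0.040 | 0.091 | 1.64 | 0.1555 | 12.5 | 84.2% |
| Raw outcome at one time | 0.05 × 1 = 0.050 | 0.114 | 1.80 | 0.1601 | 11.7 | 81.6% |

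Here 0.64 = 1 − 0.6² and 0.80 = (1 + 0.6)/2.

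**Raw scale, other treatments of the individual part.** With vI = 0.95 × 0.44 the power is 80.6%. With 0.05 added to 0.44 it is 79.8%. Simulation gives 80.9% for the raw-outcome row of the table and 79.1% for the version that adds 0.05. The raw-scale answer is therefore about 80–82%.

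**The label.** If 0.663 is entered as a variance with ICC 0.05, SE = 0.180 and power is 73.4%. That is far from 88%, so the SD was evidently used and the word is a slip.

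**Week 16 alone.** With one baseline-adjusted follow-up (variance 0.64) and vT = 0.05: a = 0.05/6 + 0.59/48 = 0.020625, b = 0.64/48 = 0.013333, SE = 0.184, noncentrality 2.71, df 13.0, power about 71%. The percentages in the table therefore describe the average of both follow-ups, not the 16-week endpoint.

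**The case against.** **The ICC's scale is unknown.** The cited source is not at hand and the article does not say. If that source reports an ICC conditional on baseline and averaging, 88% is right. This stands, and it is why the conclusion is conditional. A reader might infer that the power is simply overstated, or that therapist variance is understated by a factor of 2.3 (0.05/0.022). That factor is the raw-scale extreme; it is 0.032/0.022 = 1.45 for one baseline-adjusted follow-up and 1 for a fully conditional ICC.

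**Another route leads to 88%.** A normal approximation with therapist variance 0.05 gives 87.8%, so the printed result alone does not prove that 0.022 was used. This stands as a caution. However, the listed inputs pair 0.05 with the adjusted quantity; with those inputs the normal approximation gives 92.6%, and it ignores the small-sample correction planned in {20a}.

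**Averaging might reduce therapist variance.** If therapist effects fade or change between weeks 16 and 28, it would. This stands as a fact about the world, but the planned model assumes a constant effect, and the power calculation should agree with the model. The baseline half of the argument does not need this assumption.

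**The label is harmless.** The preceding paragraph calls 0.663 a standard deviation, and the SD was used. A reader might take the literal reading to mean a true power of 73%; the documents do not support that, because it is not the calculation that was made.

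**Little follows in practice.** The analysis model already contains the therapist effect and a small-sample correction, so inference is unaffected, and power for the two-follow-up average stays near 80% at worst. This stands and limits the weight of the point.

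**Conclusion.** The point holds in conditional form. Step 2 applies the ICC to a variance already reduced to 0.44, and that is correct only if the cited 0.05 is itself conditional on baseline and on averaging. The article does not say so. Depending on the ICC's scale, power for the average of both follow-ups is 88–89%, 86%, 84% or 80–82%. The lowest range applies if 0.05 is on the raw scale used for d = 0.5; the loss is then about 6 to 9 points from the recomputed 88.7%.

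This rests on the plan's other inputs, a two-sided 5% test with Satterthwaite degrees of freedom, and a therapist effect constant over both follow-ups as modelled in {20a}. It does not show that the design is inadequate or that the plan's arithmetic fails: 88% reproduces from the stated inputs. Nor does it make 82% the power for the 16-week primary endpoint, which on the raw-scale reading is about 71%. The variance label for 0.663 is a definite but inconsequential error.

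**What to change.** In Sample size {14}:

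1. State the scale of the cited ICC.
2. Enter the therapist variance on that scale and restate the power. If the ICC is for the raw outcome, use therapist variance 0.05 (conditional ICC 0.05/0.44 = 0.114), which gives about 80–82%. If it is already conditional on baseline and averaging, say so and keep 88%.
3. State that this figure is for the average of both follow-ups and not for the 16-week endpoint alone.
4. Name the method and degrees of freedom used.
5. Describe 0.663 as the adjusted SD, with variance 0.44.

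The cost is a reworded paragraph and possibly a less favourable stated power. The sample size stays at 130, and the analysis model is unchanged.

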### Recruitment {15}

Participants will be recruited through referrals from the Care Coordinators (CC) of psychosis patients (or other appropriate members of the clinical team) in the three sites. CCs will be given a Participant Information Sheet (PIS) and referral forms when first approached about the study by an RA. CCs will be asked to share the PIS during face-to-face and remote consultations with any patients who are potentially eligible for the study. If a patient shows an interest in the study and gives their verbal agreement to be contacted by an RA, the CC will be asked to facilitate the completion of a referral form. Once a referral has been received by the research team, the potential participant will be contacted by the RA to discuss the study further and arrange a consent and eligibility meeting. The potential participant will have a copy of the PIS at least 24 h before the consent and eligibility meeting, so they will have time to read the information, discuss it with friends and family, and formulate any questions they may have.

The consent and eligibility meeting will be completed face-to-face, unless a patient expresses a preference for a remote meeting. At this meeting, potential participants will read through the PIS with the RA to ensure they have understood the study and can ask questions. Potential participants will be invited to consent to take part in the study by reading and signing three copies of the consent form: one for the research study to be filed in the study file, one for the participant to keep and one for the participant’s care team to be emailed to the Care Coordinator and uploaded to the electronic health records. If the meeting is conducted remotely, the patient will consent verbally, and three copies of the consent form will be completed and distributed by the RA.

Eligibility data will be entered into an online platform (called REDCap) during the meeting and be accessible by the Brighton & Sussex Clinical Trials Unit (CTU). Patients will be offered reimbursement of £20 for attending the consent and eligibility meeting and travel expenses will be made available.

An additional recruitment strategy at the Sussex site will involve the use of the Everyone Counts scheme. SPFT has the Everyone Counts scheme in place for consent to contact patients about research opportunities directly. The Everyone Counts scheme is viewed as being a task in the public interest and as such has been approved by the SPFT Trust Board after consultation with the Information Governance Lead. Members of the Research & Development Department will contact potentially eligible patients to discuss the study and invite them to take part. The report of potential participants is only accessible to a limited number of authorised individuals in the R&D Department. Interested patients will be able to contact either the R&D Department or the research team directly and enquire about the study. They will be invited to discuss the study with their CC who can then complete a referral form. The research team could support potential participants to discuss the study with their CC if this is needed.

An additional strategy will be used in PCFT, whereby individuals who have participated in other trials within the Trust and have given consent to be contacted about future studies may be contacted.

## Assignment of interventions: allocation

### Sequence generation {16a} and Concealment mechanism {16b}

The CTU will set up the online randomisation process. The RAs, the Trial Statistician and the CTU Statistician will be blind to participant allocation. Following the baseline assessment, participants will be randomised, stratified by site, by the TM in permuted blocks of randomly varying length using the online randomisation module of REDCap and allocated to one of the trial arms. The next allocation is only revealed upon request. Further, the permuted blocks make the next allocation almost impossible to guess.

### Implementation {16c}

The TM will communicate the allocation to the appropriate unblinded members of the research team. An unblinded member of the research team will then contact the participant by telephone to inform them of their group allocation. APs will be notified by the TM about the participants who are allocated to the GiVE arm and will be asked to arrange a first appointment, if possible, within two weeks following the randomisation.

## Assignment of interventions: Blinding

### Who will be blinded? {17a}

The CTU will set up the online randomisation process. The RAs, the Trial Statistician and the CTU Statistician will be blind to participant allocation. Measures to maintain blinding will include: (1) participants being reminded at the beginning of each assessment interview to not disclose the arm to which they have been allocated; (2) blinded members of the research team being shielded from discussion of participants in forums where the possibility of determining participant allocation could occur; (3) researcher access to electronic health records being restricted; and (4) consideration given to office allocation and all administrative processes of blinded-vs-unblinded members of the research team. ‘Blind’ awareness and education will be promoted throughout the study. To test the success of blinding, the RA who assesses each participant will be asked to guess the allocation group for the participant at the end of the final assessment. Reported breaks in blinding will be recorded.

### Procedure for unblinding if needed {17b}

If unblinding occurs at the beginning of an assessment, the assessment will be re-blinded by re-allocating a ‘blind’ RA to collect and score study data wherever possible.

## Data collection and management

### Plans for assessment and collection of outcomes {18a}

See Fig. 2 for details of assessment at each visit.

**Fig. 2 Fig2:**
[figure not shown]
Details of assessments at each visit

### Screening measures

The assessment of eligibility in relation to the inclusion and exclusion criteria will be supported by the use of the Psychotic Symptoms Rating Scale (PSYRATS-AH) [21] (described below).

### Clinical measures—primary

Psychotic Symptoms Rating Scale (PSYRATS-AH) [21] Distress Scale – PSYRATS-AH is an 11-item rating scale designed to measure the severity of different dimensions of the voice hearing experience. Items are grouped together in four factors [40]; distress (negative content, distress, and control), frequency (frequency, duration, and disruption), attribution (location and origin of voices), and loudness (loudness item only). The ‘distress’ subscale measures the impact that voices have on the individual. The measure has established psychometric properties. The primary outcome will be measured at 16 weeks post-randomisation.

### Clinical measures—secondary

Secondary outcomes will evaluate: 1) the characteristics of voice hearing experiences (PSYRATS subscales of attribution [2 items], loudness [1 item] and frequency [3 items]); 2) mental health problems commonly experienced by people with psychosis (anxiety and depression [Hospital Anxiety and Depression Scale] [30] and paranoia [Paranoid Thoughts Scale] [35]): 3) variables that have been associated with the impact of voice hearing (negative beliefs about the self [Self Scale of the Brief Core Schema Scale] [32], negative beliefs about voices [Beliefs About Voices Questionnaire – Revised] [34], and negative relating to voices [Approve -Voices] [34] and other people [Approve-Social] [33]; and 4) personal and social recovery-oriented outcomes (goals for the outcome of CBTp [CHOICE – short form] [31].

### Health economic measures

#### EQ5D-5L [36]

EQ5D-5L [36] is a standardised instrument used as a measure of health-related quality of life that can be used in a wide range of health conditions and treatments. The descriptive system comprises five dimensions: mobility, self-care, usual activities, pain/discomfort and anxiety/depression. Each dimension has five levels: no problems, slight problems, moderate problems, severe problems and extreme problems.

#### Client Service Receipt Inventory (CSRI-UK) [29]

Client Service Receipt Inventory (CSRI-UK) [29] is a well validated adaptable research instrument used in mental health settings to collect information on health, social and voluntary service utilisation, informal care, accommodation, other public services (e.g. police) and private out-of-pocket expenses incurred. Its primary purpose is to allow resource-use patterns to be described and costs to be estimated.

#### Short Form 12 (SF12) [3]

This generic health survey captures information about functional health and well-being from the patient’s point of view.

### Plans to promote participant retention and complete follow-up {18b}

Efforts will be made to engage all participants in follow-up assessments. RAs will flexibly engage patients, offering appointments at times and locations which best suit participants and offering shorter and split assessment sessions as needed. Participants will be offered reimbursement of £20 per assessment point (i.e., eligibility, baseline, 16 and 28 weeks) and travel expenses will be made available. Retention rates will be monitored by the TM at least weekly and the research team on a monthly basis throughout the trial. The Lived Experience Advisory Panel (LEAP) will be asked to provide consultation regarding retention rates as part of their oversight role.

### Data management {19}

The research team adhere to the good practice, standards and principles which are set out in the Sussex Partnership Policy for Data Protection, Security and Confidentiality. This policy reflects the recommendations from current legislation, including The Caldicott Report (1997), the British Standard (ISO IEC 27002) for Information Security, the General Data Protection Regulation 2018 and the Sussex Partnership NHS Foundation Trust Research Policy 2021.

Data management and analysis will be in accordance with CTU Standard Operating Procedures (SOPs). Processes to promote data quality will be guided by the CTU Data Management Plans (available upon request from the first author).

All research will be carried out under the above standards and will be reviewed by an NHS Ethics Committee, the Health Research Authority and the respective R&D Department under the UK Framework for Health and Social Care Research (2017).

All members of the research team and any other individuals from collaborating Trusts or Universities involved in collecting, inputting, processing, using and sharing data will have had Information Governance Training.

The management of the data will be a standing item on the agenda of the monthly meeting of the research team.

### Confidentiality {27}

Consent forms will be stored in locked filing cabinets on NHS premises.

Participants’ names will be included on consent forms during the eligibility assessment. Following this, the RA will provide each participant with a unique study identification code. The participant’s name and unique study identification will be separated. A separate participant identification log linking participants’ names and personal details to the unique study identification codes will be kept securely at each site; this file will be kept in a password-protected file on an NHS trust computer that only members of the research team will have access to.

Quantitative data collected using REDCap will be pseudonymised by using the unique study identification codes. REDCap data is stored securely on the University of Sussex servers and is regularly backed up. Access to REDCap will be limited to the research team.

The adherence data will be collected using an audio recording device. Once the data has been collected, it will be stored on a computer that is password-protected, within a password-protected file and deleted from the audio recording device. The transcripts of the interviews will also be kept in password-protected files. The transcripts will not contain any identifiable information.

All electronically stored data (i.e., REDCap file with questionnaire scores and audio files) will be anonymised, and kept in encrypted files, on a shared drive, with access to the shared drive via username and password. Only members of the research team will have usernames and know the password and will therefore be able to access the electronic data.

All paper records of research data will be archived and then destroyed after 10 years.

All personal information will be destroyed when it is no longer needed.

### Plans for collection, laboratory evaluation and storage of biological specimens for genetic or molecular analysis in this trial/future use {33}

N/A There will be no biological specimens collected.

## Statistical methods

### Statistical methods for primary and secondary outcomes {20a}

Participant flow through the trial will be shown in a chart according to the CONSORT Statement 2010. Baseline sociodemographic characteristics and outcomes will be summarised by trial arm using descriptive statistics appropriate to distribution. The primary analysis will be conducted using a mixed effects model with clustering by therapist in the intervention group only and control participants forming their own clusters of size 1. We will include fixed effects for PSYRATS-AH Distress at baseline, the stratification variable (site) and allocation and a random effect for therapist/control participant and a random effect to account for repeated observations within participants. A small sample correction (e.g. Satterthwaite’s) will be applied due to the small number of therapists. We will report the adjusted difference in mean PSYRATS-AH Distress between arms, its 95% confidence interval and p value at each time point. Statistical significance is set at the 5% level.

Secondary outcomes will be analysed using mixed effects models appropriate to outcome distribution controlling for baseline voice hearing distress (PSYRATS-AH). A detailed statistical analysis plan will be written by the CTU Statistician and Trial Statistician, agreed with the research team and reviewed by the Trial Steering Committee (TSC).

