#### Clinical measures

3.Primary outcome: Psychotic Symptoms Rating Scale – Auditory Hallucinations (PSYRATS-AH) [21]◦ The 5-item ‘distress’ subscale measures the impact that voices have on the individual and will be the primary outcome◦ The subscale is an observer rated measure that consists of 5 items◦ This measure is included as the study intervention aims to reduce the distress associated with hearing voices◦ The primary endpoint will be 16 weeks post-randomisation.

4.Secondary (clinical) outcome: Psychotic Symptoms Rating Scale—Auditory Hallucinations (PSYRATS-AH) [21]◦ The subscales of attribution (2 items), loudness (1 item) and frequency (3 items) measure the characteristics of voices beyond distress.◦ These characteristics are not targeted by the intervention but can change during therapy.

5.Secondary (clinical) outcome: The Hospital Anxiety and Depression Scale (HADS) [30]◦ Any changes in distress related to voice hearing experience may reflect a more global reduction in emotional distress—therefore this measure will allow such changes to be captured.

6.Secondary (clinical) outcome: CHoice of Outcome In Cbt for psychosEs (CHOICE) [31]◦ The CHOICE was developed in partnership with patients to measure recovery and therefore reflects the outcomes that are important to them◦ The 12-item short form of this measure will be used.

7.Secondary (mechanism) outcome: The Brief Core Schema Scale (BCSS)—self scale [32]◦ One of the modules within the GiVE intervention focuses on beliefs about the self. This 12-item measure assesses the degree of positive and negative beliefs the person has about themselves

8.Secondary (mechanism) outcome: Approve – Voices [33]One of the modules within the GiVE intervention focusses on relationships. This 15-item measure assesses the styles of relating to voices across three subscales—assertive, aggressive and passive.

9.Secondary (mechanism) outcome: Approve—Social [33]One of the modules within the GiVE intervention focusses on relationships. This 15-item measure assesses the styles of relating to other people across three subscales—assertive, aggressive and passive.

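### The primary model as listed gives one effect averaged over 16 and 28 weeks, which contradicts the 16-week primary endpoint and the promised results at each time point; the 88% power belongs to that average too

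*Protocol article*

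**What the plan says.** The section on statistical methods for primary and secondary outcomes {20a} names the fixed effects of the primary model: "We will include fixed effects for PSYRATS-AH Distress at baseline, the stratification variable (site) and allocation". The random effects are one for therapist (each control participant being a cluster of size 1) and "a random effect to account for repeated observations within participants". Baseline is a covariate, so the repeated observations are the follow-up scores. The retention section {18b} lists the visits: "Participants will be offered reimbursement of £20 per assessment point (i.e., eligibility, baseline, 16 and 28 weeks".

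Section {20a} then commits to reporting the adjusted mean difference between arms with "its 95% confidence interval and p value at each time point". Under Clinical measures in the outcomes section {12}: "The primary endpoint will be 16 weeks post-randomisation". The data collection section repeats it: "The primary outcome will be measured at 16 weeks post-randomisation".

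The sample size section {14} asks for 90% power at the 5% level when d = 0.5, and its first step takes both follow-up visits together: "with one baseline measure and two follow-up measures, with correlation between these of 0.6". It obtains 37 per arm and an adjusted SD of 0.663. It then allows for therapist clustering in the GiVE arm (6 therapists with 8 completers each, ICC 0.05, 48 unclustered controls) and states 88% power.

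**The concern.** A mixed model with one allocation coefficient and no time terms gives one between-arm difference. It has no parameter from which to estimate separate differences at 16 and 28 weeks, and none that isolates 16 weeks. The listed model therefore conflicts with the reporting commitment in the same section and with the declared primary endpoint.

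What is at stake is which quantity the primary p value tests. The average and the 16-week effect agree only if the effect is the same at both visits. The article gives no expected effect at 28 weeks, and the feasibility signal against usual care that it cites (d = 0.49) is for 16 weeks only. The power statement is affected too, because it was computed for the more precise two-visit average.

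**Working it through.** **Inputs, all from the sample size section {14}:** d = 0.5; correlation r = 0.6 between measures; one baseline and two follow-ups; 6 therapists × 8 = 48 completers in the GiVE arm; 48 controls; ICC 0.05 (GiVE arm only); 5% significance.

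**Assumptions:** two-sided test (sidedness is not stated), equal correlations of 0.6, the same ICC for a single-visit contrast, complete data at both follow-ups.

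**1. Reproduce the plan's figures.**
- Variance factor for the mean of two follow-ups adjusted for baseline: (1 + r)/2 − r² = 0.80 − 0.36 = 0.44. SD = √0.44 = 0.663, as stated.
- n per arm = 2 × 0.44 × (1.960 + 1.282)² / 0.5² = 37, as stated.
- Design effect in the GiVE arm: 1 + (8 − 1) × 0.05 = 1.35.
- SE² = 0.44 × 1.35/48 + 0.44/48 = 0.012375 + 0.009167 = 0.021542, so SE = 0.147.
- Satterthwaite df = 0.021542² / (0.012375²/5 + 0.009167²/47) = 14.3.
- Noncentrality 0.5/0.147 = 3.41. Noncentral-t power is 88.7%, or 87.6% if the therapist variance is added on top of the residual variance. The stated figure is 88%.

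The plan's figures therefore reproduce, and they are figures for the mean of both follow-ups. Section {14} calls 0.663 an SD in one place and a variance in another; 88% reproduces only when it is used as an SD.

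**2. What the listed model estimates.** With complete data at both visits, the single allocation coefficient is (d16 + d28)/2. As a check, data were simulated with 48 per arm, r = 0.6, no therapist clustering, and assumed effects of 0.5 at 16 weeks and 0.1 at 28 weeks. A least-squares fit without time terms returned 0.30. Adding time and allocation-by-time returned 0.50 and 0.09.

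**3. Effect and power of the averaged test**, with d16 = 0.5, SE 0.147 and df 14.3. The 28-week values are assumptions.

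| d at 28 weeks | Averaged coefficient | Power |
|---|---|---|
| 0.50 (sustained) | 0.50 | 88.7% |
| 0.25 (halved) | 0.375 | 66% |
| 0 (gone) | 0.25 | 36% |

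**4. Power of a 16-week contrast.**
- Variance factor for one follow-up: 1 − r² = 1 − 0.36 = 0.64; SD = 0.80.
- n per arm for 90% power under simple randomisation: 2 × 0.64 × (1.960 + 1.282)² / 0.5² = 53.8, so 54 instead of 37.
- With clustering: SE² = 0.64 × 1.35/48 + 0.64/48 = 0.03133, SE = 0.177, noncentrality 2.82, df 14.3. Power is 75%, or 73% with the therapist variance added on top. By normal approximation it is 81% or 79%.

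**The case against.** The strongest reply is that the list is not declared closed. The text says what will be included, not that nothing else will be. The reporting sentence shows that time-specific estimates are intended, no passage says that an averaged coefficient will be reported or will decide the trial, and a detailed analysis plan, not shown here, is announced. All of this stands as evidence of intent. It does not remove the contradiction: the article chose to list the terms of its primary model, that list cannot produce the promised results, and the random effect for repeated observations makes separate models per visit an unlikely reading. The sample size, moreover, is consistent with the average and not with 16 weeks.

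Stronger readings are tempting and should be resisted.
- A reader might infer that the primary p value will in fact be for the averaged effect. The documents do not establish this, because the reporting sentence points the other way.
- A reader might infer that a waning effect will be hidden, or a late one passed off as a 16-week benefit. That would require the analysts to ignore their own commitment to results at each visit. The 66% and 36% figures also rest on assumed trajectories.
- A reader might blame the missing time main effect on its own. With complete data at both visits, time is balanced across arms, so omitting it does not bias the allocation coefficient, and between-arm precision rests mainly on participant means. The allocation-by-time term is the one that matters.

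**Conclusion.** The contradiction is real. Section {20a} lists a model whose only treatment parameter is an average over 16 and 28 weeks, while the same section promises results per visit and sections {12} and {18a} place the primary outcome at 16 weeks. This is a stated rule that yields the wrong quantity, not a detail left to the analysis plan.

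Its size depends on the course of the effect. If d = 0.5 is sustained, the two quantities coincide and nothing is lost in the estimate. If the effect halves or disappears by 28 weeks, the averaged coefficient is 25% or 50% below the 16-week effect.

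The consequence for the power statement does not depend on the trajectory: on the plan's inputs and the assumptions listed in the working, 88% becomes about 75% for the 16-week contrast with the small-sample correction that the plan itself proposes.

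**What to change.** In section {20a}, add time (16 and 28 weeks) and allocation-by-time to the fixed effects. Name the allocation contrast at 16 weeks as the single primary test, and the 28-week contrast from the same model as secondary. Keep the therapist and participant random effects and the small-sample correction. A baseline-by-time term is a reasonable option but is not needed to resolve the contradiction. Make the analysis plan agree.

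In section {14}, restate the power for the 16-week contrast (about 75% with Satterthwaite df on the present inputs) and call 0.663 an SD throughout.

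The cost is a sentence of text, a few more model parameters, and a less favourable stated power. If the sponsor does intend the two-visit average as the primary quantity, the endpoint and reporting statements would have to change instead, and the article should then say so openly.
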